## 2. GENERAL INFORMATION

### ***Trial Identification***

Protocol Code: SARTRE

EUDRACT: 2020-002037-15

Version and Date: v 2.0 of May 5th 2020

Title of the trial: Multicenter, randomized, open-label study to evaluate the efficacy and safety of SOC + sarilumab versus Standard of Care for the Early Treatment of COVID-19-pneumonia in Hospitalized Patients.

### ***Centers of the Trial***

This will be a multicenter national study, with Hospital Universitario Puerta de Hierro Majadahonda acting as Study Site Coordinator. The list of participating centers can be found attached as Appendix 7.

### ***Expected duration of the Trial***

Expected recruitment will take 2 months since first site initial visit, which will follow the approval of the AEMPS.

Each patient will participate in the trial for a maximum of 29 days, including a screening phase of 1 day, treatment duration of 1-2 day, initial follow-up and a follow-up visit at 28 days from randomisation.

### ***Patient Number***

Two hundred patients

## **3. BACKGROUND AND RATIONALE FOR THE STUDY**

### ***Drug Information***

Kevzara® (sarilumab) is a fully human IgG1 monoclonal antibody that binds specifically to both soluble and membrane-bound IL-6 receptors (sIL-6Rα and mIL-6Rα) and has been shown to inhibit IL-6-

mediated signaling through these receptors. IL-6 is a pleiotropic pro-inflammatory cytokine produced by a variety of cell types including T- and B-cells, lymphocytes, monocytes and fibroblasts. IL-6 has been shown to be involved in diverse physiological processes such as migration and activation of T-cells, induction of immunoglobulin secretion, initiation of hepatic acute phase protein synthesis, and stimulation of hematopoietic precursor cell proliferation and differentiation.

Kevzara® (sarilumab) is authorized in the European Union for the treatment of adult patients with moderately to severely active rheumatoid arthritis (RA) who have had an inadequate response or intolerance to one or more biologic or non-biologic disease-modifying anti-rheumatic drugs (DMARDs). The recommended dose is 200 mg once every 2 weeks given as a subcutaneous injection.

### *Study rationale*

In some patients, acute, life-threatening respiratory injury produced by viruses such as SARS-CoV and other viral pneumonia are associated with an over-exuberant cytokine release. Elevated levels of blood IL-6 had been identified as a one of the risk factors associated with severe COVID-19 disease. Preliminary experiences with tocilizumab, an anti-IL6 inhibitor, show promising results with improvements seen in clinical symptoms, respiratory function, and inflammatory laboratory parameters.

Based on this and on current knowledge on the role of the anti-IL6 inhibitor tocilizumab in the treatment of cytokine release syndrome associated to CART therapies, tocilizumab is being extensively used nowadays in clinical practice, and many clinical trials are being conducted around the world, for preventing the fatal consequences of acute respiratory and multi organ failure associated with acute respiratory syndrome due to severe COVID-19 infection.

In Spain, anti-IL6 inhibitors are among the therapeutic armamentarium for preventing the fatal consequences of acute respiratory and multi organ failure in around 20% of the COVID-19 infected patients. At present, their use is prioritized to patients with severe interstitial pneumonia (COVID2-3) with hyperinflammation as determined by the presence of elevated IL6 and/or d-dimer, or progressive d-dimer increase, in patients who otherwise are subsidiary to ICU admission.

Preliminary results of an unpublished ongoing multicenter, national, observational cohorts Study conducted in patients treated with tocilizumab vs matched controls led by the same local investigation team suggest that IL-6 inhibitors may prevent progression to ICU admission or death in patients with severe COVID-19 interstitial pneumonia and that there is a window of opportunity for this drug, yet to be determined.

However, many uncertainties remain on the actual role of anti-IL6 inhibitors in this setting, and whether current use and timing is the right one. Among clinicians there is the hypothesis that the use of anti-IL6 inhibitors at an earlier state during the hyperinflammatory syndrome than the current one would be beneficial and may avoid progressing to ARDS.

On the other hand, the standard of care has changed in the prior weeks and nowadays the use of corticosteroids has become part of the SOC in the treatment of COVID-19 pneumonia, and our limited experience suggests that better treatment outcomes can be achieved when combining IL6-inhibitors with corticosteroids. Thus, the question still remains on whether anti-IL6 inhibitors concomitantly with corticosteroids may potentiate the anti-inflammatory response and lead to better treatment outcomes.

### *Hypothesis*

The hypothesis of this trial is that in patients with pneumonia and respiratory failure caused in the setting of COVID-19, an early blockade of IL-6 with sarilumab plus weight adjusted corticosteroid doses plus SOC, will attenuate the cytokine storm and halt the progression to acute respiratory distress syndrome (ARDS) and the need for mechanical ventilation, ICU admission, or death.

#### 4. TRIAL OBJECTIVES

##### *Primary Objective*

The overall objective of the study is to evaluate the efficacy of an early intervention with sarilumab in the prevention of progression to severe respiratory failure/ICU admission or death in COVID-19 infected patients with pneumonia and regular oxygen supplement requirements (Brescia-COVID- 1).

##### *Secondary Objectives*

1. To assess differences between both strategies in the following:
  - Time to respiratory failure
  - Time to reduction of supplemental oxygen requirements
  - Time to mechanical non-invasive or invasive ventilation.
  - The duration of hospitalization
  - Mortality rate and survival.
  - Rate of ICU admission
  - To evaluate the efficacy of sarilumab in COVID-19 infected patients with pneumonia Brescia-COVID  $\geq 2$  (open-label follow up phase).
2. To evaluate safety of sarilumab treatment in treating patients with COVID-19 pneumonia.
3. To evaluate differences in the effect of sarilumab on the serum levels of inflammatory cytokines in patients with COVID-19.
4. To evaluate differences in the proportion of patients showing more than >1 organ failure, e.g. cardiovascular, liver and kidney failure
5. To identify prognosis factors of sarilumab efficacy related to laboratory parameters or disease features

##### *Objectives and endpoints*

Table 1 - Objectives and endpoints

| OBJECTIVES                                                                                                                                                                     | ENDPOINTS AND OUTCOME MEASURES                                                                                                                                                                 |
|--------------------------------------------------------------------------------------------------------------------------------------------------------------------------------|------------------------------------------------------------------------------------------------------------------------------------------------------------------------------------------------|
| PRIMARY                                                                                                                                                                 |                                                                                                                                                                                                |
| Evaluate the efficacy of an early intervention with sarilumab in COVID-19 infected patients with pneumonia and regular oxygen supplement requirements (Brescia-COVID 1) | The primary endpoint is the proportion of patients progressing to severe respiratory failure (Brescia-COVID $\geq 2$ ), ICU admission or death from randomization up to day 15th of follow-up. |
| SECONDARY                                                                                                                                                               |                                                                                                                                                                                                |

---

**Evaluate effects of efficacy of an early intervention with sarilumab on secondary efficacy endpoints as compared to standard of care as assessed by:**

|                                                                                                                                                                                                                                                                                                                                                                                                                                                        |                                                                                                                                                                                                                                                                                                                                                                                                                                                                                                                                                                                                                                                                                                                                                                                                                    |
|--------------------------------------------------------------------------------------------------------------------------------------------------------------------------------------------------------------------------------------------------------------------------------------------------------------------------------------------------------------------------------------------------------------------------------------------------------|--------------------------------------------------------------------------------------------------------------------------------------------------------------------------------------------------------------------------------------------------------------------------------------------------------------------------------------------------------------------------------------------------------------------------------------------------------------------------------------------------------------------------------------------------------------------------------------------------------------------------------------------------------------------------------------------------------------------------------------------------------------------------------------------------------------------|
| 
 
• Clinical Severity: progression to severe respiratory failure/ICU admission or death
 
                                                                                                                                                                                                                                                                                                                | 
Time to respiratory failure
Rate of ICU admission
Rate of mortality
                                                                                                                                                                                                                                                                                                                                                                                                                                                                                                                                                                                                                                                                                                                                 |
| 
 
• Oxygenation: 
 
○ Oxygenation free days in the first 15 days
 
○ Incidence and duration of new oxygen use during the study
 
○ Mechanical Ventilation 
 
• Ventilator free days in the 15 days.
 
• Incidence and duration of new mechanical ventilation use during the study
 
 
 
 
 
 | 
Time to reduction of supplemental oxygen requirements
Time to non-invasive or invasive ventilation.
 
Proportion of patients with at least 1 point progression in the 7-point ordinal scale from baseline up to day 15
Ordinal scale:
 
 
1) Not hospitalized, no limitations on activities.
 
2) Not hospitalized, limitation on activities.
 
3) Hospitalized, not requiring supplemental oxygen.
 
4) Hospitalized, requiring supplemental oxygen.
 
5) Hospitalized, on non-invasive ventilation or high flow oxygen devices or oxygen mask with reservoir bag.
 
6) Hospitalized, on invasive mechanical ventilation or ECMO.
 
7) Death.
 
 |
| 
 
• Hospitalization
 
• Mortality 
 
○ 15-day mortality
 
 
 
                                                                                                                                                                                                                                                                                         | 
Duration of hospitalization.
 
Date and cause of death (if applicable).
                                                                                                                                                                                                                                                                                                                                                                                                                                                                                                                                                                                                                                                                                                                                |

---

**Evaluate the efficacy of sarilumab in in COVID-19 infected patients with pneumonia Brescia-COVID-  $\geq 2$  (open-label follow up phase).**

Rate of ICU admission  
Rate of mortality

---

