### ***Exclusion Criteria***

1. Patients with high oxygen requirements including face mask with reservoir, non-invasive mechanical ventilation or high flow nasal cannula, or mechanical ventilation.
2. Patients admitted at the ICU
3. Participation in any other clinical trial of an experimental treatment for COVID-19.
4. In the opinion of the clinical team, progression to death is imminent and inevitable within the next 24 hours, irrespective of the provision of treatments.
5. Any hypersensitivity or allergy to the administration of sarilumab or corticosteroids.
6. Current treatment with immunosuppressive or any immunomodulatory medication within 8 weeks of baseline.
7. Patients who have received immunosuppressive antibody therapy within the past 5 months, including intravenous immunoglobulin
8. AST/ALT values > 10 x ULN
9. Neutropenia (< 0.5 x 10^9/L).
10. Severe thrombocytopenia (< 50 x 10^9/L).
11. Sepsis caused by an alternative pathogen.
12. Diverticulitis with risk of perforation.
13. Ongoing infectious dermatitis.
14. Patients with another active infection, including localized infections.
15. Pregnant or breast-feeding females will be excluded

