### ***Sample size estimation***

To obtain a power of 80.00% to detect differences in the contrast of the null hypothesis  $H_0: p_1 = p_2$  by means of a bilateral Chi square test for two independent samples, taking into account that the level of significance is 5.00%, and assuming that the proportion in the Reference group is 25.00%, the proportion in the Experimental group is 10.00%, and that the proportion of experimental units in the Reference group with respect to the total is 50.00 % it will be necessary to include 100 experimental units in the Reference group and 100 units in the Experimental group, totalling 200 experimental units in the study.

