#### ***Shift outcomes***

The median of the absolute values the 95% confidence interval (95%CI) will be calculated using the Hodges-Lehmann methods (i.e. median of all cross differences between treatments based on the Mann-Whitney distribution).

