#### *General strategy for the rest of variables*

The rest of variables will be analysed according to the following strategy: The Fisher's exact test used for categorical variables, the t-test for Gaussian distributed variables and, for non-Gaussian continuous or ordinal variables, non-parametric methods (Mann-Whitney test).

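### Table 1 compares the arms on how long new mechanical ventilation lasts, which can be measured only in patients ventilated after randomisation and is shortened by death

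*Protocol*

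**What the plan says.** The secondary block of Table 1 (protocol section 4, Objectives and endpoints) evaluates early sarilumab "on secondary efficacy endpoints as compared to standard of care as assessed by" a list of items. Under mechanical ventilation the list has two: "Ventilator free days in the 15 days" and "Incidence and duration of new mechanical ventilation use during the study". Both stand in the left-hand (objectives) column. The right-hand column for that row gives other measures, among them "Time to non-invasive or invasive ventilation" and progression on the 7-point ordinal scale.

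Section 6 excludes "Patients with high oxygen requirements including face mask with reservoir, non-invasive mechanical ventilation or high flow nasal cannula, or mechanical ventilation", so every episode of ventilation begins after entry.

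Section 10 gives default tests for variables that it does not treat individually, including "for non-Gaussian continuous or ordinal variables, non-parametric methods (Mann-Whitney test)". Its missing-data paragraph counts missing binary outcomes as failures. Neither rule says what value a never-ventilated patient has for duration, or how a death on the ventilator counts.

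**The concern.** Incidence is named separately in the same phrase, and the all-patient measure, ventilator-free days, is the item above it. The duration of new use therefore reads most naturally as duration among those newly ventilated.

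Two problems follow. First, membership of that group is an outcome. If the drug keeps the milder cases off the ventilator, the sarilumab patients who remain are the more severe ones and their episodes are longer, so an effective drug looks harmful. Second, a patient who dies early on the ventilator contributes a short duration, which looks like benefit. Randomisation protects against neither. At stake is a supporting statement in the report about ventilation that could contradict the true effect.

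**Working it through.** **The plan's own figures.** The only rates in the protocol are those for the primary composite: "the proportion in the Reference group is 25.00%, the proportion in the Experimental group is 10.00"%. The pooled two-sided formula with mean rate 0.175 gives

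n = (1.960 × √(2 × 0.175 × 0.825) + 0.842 × √(0.25 × 0.75 + 0.10 × 0.90))² / 0.15² = 99.5, so 100 per arm.

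The planned 200 patients are reproduced. The protocol states no ventilation incidence or duration, so everything below rests on assumed values.

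**Selection into the ventilated group.** Assume 15% of controls are ventilated, natural duration is exponential with mean 6 days and capped at 15 days, and sarilumab prevents every episode that would last under 3 days and no other.

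- Control, mean among the ventilated: 6 × (1 − e^(−15/6)) = 5.5 days.
- Share of episodes lasting 3 days or more: e^(−3/6) = 0.607. About 15 controls and 15 × 0.607 = 9 sarilumab patients per 100 are ventilated.
- Sarilumab, mean among the ventilated: 3 + 6 × (1 − e^(−12/6)) = 8.2 days.
- Apparent harm: 8.2 − 5.5 = 2.7 days.
- Ventilator days per randomised patient: control 0.15 × 5.507 = 0.83; sarilumab 0.15 × 0.6065 × 8.188 = 0.74.

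The drug reduces ventilation, yet the contrast among the ventilated shows harm.

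**Prevention unrelated to episode length.** With the same 39% of episodes prevented at random, the means among the ventilated are 5.5 and 5.5 days. Days per randomised patient fall from 0.83 to 0.15 × 0.6065 × 5.507 = 0.50. The contrast no longer misleads on direction, but it misses the benefit.

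**Other assumptions.** Durations were also simulated as log-normal (median 7 days, log-SD 0.8, capped at 28 days), 100 patients per arm, 3,000 trials per row, with the shortest episodes prevented:

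| Ventilated, control / sarilumab | Excess mean duration on sarilumab, ventilated only | Trials with longer sarilumab mean | Mann-Whitney significant in the wrong direction |
|---|---|---|---|
| 25% / 10% | 6.6 days | 99.7% | 83% |
| 15% / 8% | 4.6 days | 93% | 42% |
| 10% / 5% | 5.0 days | 91% | 27% |

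With random prevention the mean difference was within 0.1 day of 0 in all three rows.

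**Death.** Take 10 ventilated patients per 100 randomised. Survivors are ventilated for 12 days, and those who die do so after 2 days of ventilation. With 0, 2 or 4 deaths, mean duration among the ventilated is 12.0, (2 × 2 + 8 × 12)/10 = 10.0, and (4 × 2 + 6 × 12)/10 = 8.0 days. More early deaths look better. Giving never-ventilated patients 0 days does not cure this: with 0 and 4 deaths, days per randomised patient are 1.2 and 0.8.

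**Ventilator-free days to day 15, same example.** A never-ventilated patient scores 15 and a ventilated survivor 15 − 12 = 3.

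- Death scored 0: no deaths (90 × 15 + 10 × 3)/100 = 13.80; four deaths (90 × 15 + 6 × 3)/100 = 13.68. The order is right.
- Days after death counted as ventilator-free (13 per death): 13.80 against (90 × 15 + 6 × 3 + 4 × 13)/100 = 14.20. The order is wrong, so the score for death has to be written down.

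**The case against.** The strongest reply is that duration of ventilation is not a formal endpoint. It stands in the objectives column of Table 1, appears neither in the endpoint column nor in the secondary endpoint lists of the synopsis and section 8, and no decision rests on it in a trial that section 5 calls exploratory. That stands, and it limits the severity.

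A second reply is that the protocol never restricts duration to the ventilated, and that a statistical analysis plan may score everyone else as 0. That is possible and would remove the selection problem, but not the distortion from death. It is also not the natural reading of the item.

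Third, the 2.7-day reversal needs prevention concentrated on short episodes. That is correct, and the figure is an illustration, not a forecast.

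A reader might go further and infer that the plan would hide any effect on ventilation, because a Hodges-Lehmann estimate (the "median of all cross differences between treatments based on the Mann-Whitney distribution") of ventilator-free days would be 0 when most patients score 15. The protocol does not support this. That method is given for shift outcomes, and nothing assigns ventilator-free days to that heading. Section 10 also offers means, mixed models with adjusted means, the t-test and the Mann-Whitney test. If 25% and 10% of patients are ventilated, with the exponential durations above and 100 per arm, a simulation gives the Mann-Whitney test about 81% power and a t-test about 57%.

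Nor are ventilator-free days the only ventilation measure that covers everyone randomised. Incidence, time to ventilation and the ordinal scale do so too.

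**Conclusion.** The concern holds for the duration item. On its natural reading, Table 1 sets up a comparison in a subgroup formed after randomisation, and nothing else in the protocol repairs it. Under the stated assumptions the contrast shows 5.5 against 8.2 days while true ventilator use falls from 0.83 to 0.74 days per patient. If prevention is unrelated to episode length, the contrast is about 0. Early deaths move it towards apparent benefit in either case. The direction of these distortions follows from the structure of the measure; their size depends on ventilation rates and durations that the protocol does not give.

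It does not follow that a real effect on ventilation would go unseen in this trial, since several listed measures cover all randomised patients. Severity is minor.

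**What to change.** In Table 1, state that duration of new mechanical ventilation is reported descriptively only, beside the number ventilated and the number who died. Make ventilator-free days to day 15, already listed there, the comparative measure in all randomised patients, with death by day 15 scored as 0 days. Test it with the Mann-Whitney test already named in section 10, and tabulate death and ventilation separately.

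The cost is wording in Table 1 and the statistical analysis plan, plus ventilation start and stop dates if the case report form does not already hold them. No patients or visits are added. Table 2 already records ventilator requirement to day 15, but the synopsis ends observation at ICU admission. The text should therefore say that ventilation status and death are collected to day 15 after ICU admission as well.

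The small downside is that the score mixes death with ventilation, which is why both components must be shown.
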